#### For the research team

Only the lead researcher for the trial will conduct the welcome call and will follow a welcome call script to ensure that all welcome calls are standardised to reduce potential therapeutic effects before the intervention or waitlist condition begins.

### Concomitant care permitted or prohibited during the trial {15d}

Prior to beginning treatment, all participants will be instructed to refrain from receiving other psychological treatment during the trial. Participants will be advised that trial eligibility requires that they do not start new psychotropic medications during the trial and remain on a stable dose of their current psychotropic medication if they are taking medication. All urgent and unexpected concomitant psychological interventions, treatments, and changes in medication that do occur during the trial will be documented in the research trial records as soon as the research team are made aware of this.

### Outcomes {16}

All outcomes will be measured and compared between each treatment condition, unless otherwise specified.

#### Primary outcome

Absence or presence of PTSD and MDD at 8 weeks post-random allocation, assessed with the Structured Clinical Interview for DSM-5 (SCID-5; PTSD and MDD modules) [22].

#### Secondary outcomes

PTSD symptom severity at 4 and 8 weeks post-random allocation and at 6 months post-intervention completion, measured with the PCL-5 [20].MDD symptom severity at 4 and 8 weeks post-random allocation and at 6 months post-intervention completion, measured with the PHQ-9 [21].GAD symptom severity measured at 4 and 8 weeks post-random allocation and at 6 months post-intervention completion with the Generalised Anxiety Disorder Scale (GAD-7) [28].Insomnia symptom severity measured at 8 weeks post-random allocation with the Insomnia Sleep Index (ISI) [25].C-PTSD symptom severity measured at 8 weeks post-random allocation and at 6 months post-intervention completion with the International Trauma Questionnaire (ITQ) [27].

#### Process measures

Frequency of maladaptive responses to intrusions measured at 4 and 8 weeks post-random allocation and at 6 months post-intervention completion with the Responses to Intrusions Questionnaire Short Version (RIQ-s) [29].Posttraumatic cognitions measured at 4 and 8 weeks post-random allocation and at 6 months post-intervention completion with the Posttraumatic Cognitions Inventory Short Version (PTCI-s) [31].

#### Wellbeing and resilience measures

Wellbeing measured at 8 weeks post-random allocation and at 6 months post-intervention completion with the Warwick-Edinburgh Mental Wellbeing Scale (WEMWBS) [32].Resilience measured at 8 weeks post-random allocation and at 6 months post-intervention completion with the Connor-Davidson Resilience Scale 25 (CD-RISC-25) [34].Social support from family/friends and work/colleagues at 8 weeks post-random allocation and at 6 months post-intervention completion measured with the social support scales adapted from Sarason et al. [35].Life and job satisfaction questions at 4 and 8 weeks post-random allocation and at 6 months post-intervention completion.

#### Health economic measures

This study will also collect health economics outcomes to assess resource utilisation, productivity loss, quality of life, and health status. Health economic measures will be administered at baseline, 8 weeks post-random allocation, and 6 months post-intervention completion for secondary analyses.

#### Qualitative feedback

Semi-structured interviews exploring participants’ and coaches’ experiences of the SHAPE intervention. Constructive feedback will be collected from participants and coaches about the perceived acceptability, accessibility, and suitability of SHAPE to guide future improvements to the intervention. Semi-structured interviews will take place shortly after participants complete their post-intervention telephone assessment to allow feedback to be derived that is minimally affected by the passage of time. Interviews with wellbeing coaches will take place during the period that coaches are delivering the SHAPE intervention, or shortly afterward.

### Adverse event reporting and harms {17}

Participant risk and safety will be monitored throughout the trial. A protocol for defining and recording serious adverse events (SAEs) and adverse events (AEs) has been developed for the trial that will be referred to throughout the trial (see Appendix 1). If a SAE or AE is reported from a participant, an AE or SAE report form (as appropriate) will be filled out by the safeguarding lead who is on-call and also sent to the PI to complete and review. Only SAEs will be reported to the TSC, unless an AE is recurring or has been reported more than once for a participant.

For participants assigned to the intervention condition, SAEs and AEs will be monitored through screening questionnaires, SCID-5 telephone assessments, weekly questionnaires, and during coaching calls. For participants assigned to the waitlist condition, SAEs and AEs will be monitored with the study questionnaires and SCID-5 telephone assessments at baseline, 4-week post-random allocation, and 8-week post-random allocation.

During SCID-5 telephone assessments, assessors will be asked to complete a brief risk assessment if a participant discloses suicidal ideation. After the assessment, assessors will be required to consult with the available safeguarding lead on the research team for guidance on what necessary action needs to be taken, and the PI will be informed. A SHAPE AE or SAE report form will be completed by the safeguarding lead (see Appendix 2) and PI (see Appendix 3) and safely stored in a secure online location on Nexus 365 OneDrive for Business.

During calls, coaches will be asked to notify the assigned safeguarding lead directly should they be concerned at any time that a participant has caused, or is likely to cause, significant harm to themselves or others. Coaches will conduct risk assessments if they deem a participant to be showing signs of risk during the call, or if item 9 on the PHQ-9 increases from their baseline value. If a participant is deemed to be at high risk, the study team will inform the participant’s GP with consent from the participant in order to ensure participant safety. If a coach is concerned that a participant is believed to likely cause imminent significant harm to others, they will need to pass this information onto the assigned safeguarding lead, who will be required to inform the appropriate authorities directly.

All SAEs and AEs will be reported in a reporting form (see Appendix 2 and 3) and logged in a risk and safeguarding report log that will be stored in a secure online location on Nexus 365 OneDrive for Business for the study team to access. Only the main research team members will be able to access the specific AE and SAE reports. The number and type of SAEs will be reported in the main trial publication.

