## Intervention and comparator

### Intervention and comparator description {15a}

#### SHAPE condition

After screening, assessment, and randomisation, participants randomly allocated to the intervention condition will receive the SHAPE intervention over a period of 8 weeks. SHAPE will be delivered remotely over the telephone or via audio link through Microsoft Teams, dependent on participant preference to further enhance the accessibility of SHAPE coaching and reduce potential barriers (e.g. limited access to the internet or to an electronic device, difficulties with computer literacy). Participants will receive approximately 6 coaching calls (1 call per week) with the expectation that participants or coaches may need to skip a week (due to sickness, annual leave, holidays, etc.). In circumstances where additional clinical support is warranted and would be in the participant’s clinical best interests, up to 2 more sessions can be offered (e.g. prolonged exposure to multiple traumatic events, new trauma that emerges during treatment, an ongoing court case). Coaching calls will last between 30 and 50 min and will focus on a specific tool (as outlined in Table 2).

**Table 2 Tab2:** Tools typically used in SHAPE weekly coaching calls

Core tools
1. THEN vs. NOW for re-experiencing symptoms
2. IF THEN plans for rumination
3. Planning ahead for low mood and avoidance
4. Surveys and behavioural experiments for updating unhelpful thoughts
5. Imagery to create a sense of continuity in the present with what has been lost in the past
6. Responsibility pie charts for guilt and self-blame
7. Realistic risk and worry diary for worry
8. Blueprint for beating stress and low mood

During supervision, coaches will plan their future coaching calls with their designated supervisor, who will be a clinical psychologist on the SHAPE team. Coaches and supervisors will discuss which tools would be most useful to cover in each call to address the key symptoms endorsed on the weekly PTSD and MDD symptom measures. Table 2 provides a list of the core tools typically used in the SHAPE intervention and the symptoms they target.

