#### Waitlist condition

Participants randomly allocated to the waitlist condition will not receive any therapeutic support from their assigned coach or the research team during the 8-week waiting period. Participants are asked not to take up psychological support during the waiting period (i.e. CBT, counselling) or change their current psychotropic medication if they are already taking it to allow for a clean comparison between conditions. If a participant wishes to access the SHAPE intervention, they will be able to receive the intervention after they complete their post-wait measures and have their second telephone assessment at 8 weeks post-random allocation. If a participant no longer wishes to receive the intervention, they can opt out and will be provided with relevant information on alternative services if requested.

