#### Participants in the waitlist condition

Some participants in the 8-week waitlist condition might experience worsening of symptoms during this time due to the progression of symptoms or factors such as an unexpected life event. The study team will be able to detect this in the participant’s 4-week and 8-week questionnaires. The study team will contact the participant and conduct a risk assessment if they detect an increase in risk from baseline. If it is deemed that the participant would benefit from immediate assessment or treatment from a mental health service, then the study team will withdraw the participant from the trial and refer them to the relevant support service.

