**Fig. 2 Fig2:**
[figure not shown]
Schedule for forms, measures, interventions, and assessments in the SHAPE randomised controlled trial. *6 months post-intervention for participants randomly allocated to intervention or to waitlist who then receive the intervention, or 6 months post-waitlist for participants who complete the waitlist and who do not take up the intervention. **Followed by SHAPE intervention for participants who complete the waitlist condition and who would like to receive SHAPE coaching. ***Every week participants in SHAPE coaching receive a short weekly questionnaire (i.e. PCL-5 and PHQ-9) except in week 4 when they are sent the mid-intervention questionnaire. Informed consent-1 = Informed consent for eligibility assessment; *PCL-5* = PTSD Checklist for DSM-5; *PHQ-9* = Patient Health Questionnaire; *SCID-5* = Structured Clinical Interview for DSM-5 (PTSD and MDD modules); Informed consent-2 = Informed consent for assessment/trial; *GAD-7* = Generalised Anxiety Disorder Scale; *ISI* = Insomnia Sleep Index; *PTCI-s* = Posttraumatic Cognitions Inventory short version; *RIQ-s* = Responses to Intrusions Questionnaire short version; *LEC-5* = Life Events Checklist for DSM-5; *ITQ* = International Trauma Questionnaire; *ACE-Q* = Adverse Childhood Experiences Revised Questionnaire; *WEMWBS* = Warwick-Edinburgh Mental Wellbeing Scale; *CD-RISC-25* = Connor-Davidson Resilience Scale 25; *iPCQ* = iMTA Productivity Cost Questionnaire; *SF-HLQ* = Short Form Health and Labour Questionnaire; *CSRI* = Client Service Receipt Inventory; *EQ-5D-5L* = EuroQol-5 Dimensions-5 Levels health survey; *Re-QoL* = Recovering Quality of Life Questionnaire

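### Adverse events are sought on about 15 scheduled occasions in SHAPE and 3 on the waitlist, and the harms publication commitment names neither AEs, arm nor time window

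*Protocol article*

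**What the plan says.** All references are to the protocol article.

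- **Detection in SHAPE** (Adverse event reporting and harms): "SAEs and AEs will be monitored through screening questionnaires, SCID-5 telephone assessments, weekly questionnaires, and during coaching calls".
- **Detection on the waitlist** (same section): "SAEs and AEs will be monitored with the study questionnaires and SCID-5 telephone assessments at baseline, 4-week post-random allocation, and 8-week post-random allocation".
- **Weekly forms in SHAPE** (caption of Fig. 2): "Every week participants in SHAPE coaching receive a short weekly questionnaire (i.e. PCL-5 and PHQ-9) except in week 4". In week 4 the longer mid-intervention set replaces the short form.
- **Calls in SHAPE** (SHAPE condition): about 6 weekly coaching calls, with up to 2 more where warranted.
- **Waitlist contact** (Waitlist condition): participants "will not receive any therapeutic support from their assigned coach or the research team during the 8-week waiting period". On worsening, the section on discontinuing or modifying the allocated condition says of waitlist participants: "The study team will be able to detect this in the participant’s 4-week and 8-week questionnaires".
- **Recording and publication** (Adverse event reporting and harms): every AE and SAE goes on a form and into a log. The publication sentence is "The number and type of SAEs will be reported in the main trial publication". The Trial Steering Committee, which also acts as the data monitoring committee, receives SAEs, and receives AEs only if they recur or are reported more than once for a participant.

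The heading of the statistical methods section mentions harms, but the text below it describes no harms comparison.

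**The concern.** A recorded event count is the product of how often events occur and how often anyone looks. Here the second factor differs by arm by design. If counts from the two arms are set side by side, part of any excess in SHAPE reflects closer observation, and the waitlist count is an under-count. A reader cannot separate the two unless the report says how each event was found.

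The publication sentence does not help. It fixes no arm and no time window, although waitlist participants may receive SHAPE after week 8. Without a window, events during their later coaching could be mixed with events from the randomised period. The rule for passing AEs to the steering committee also depends on repeat reports, which are likelier where contact is more frequent.

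At stake is the interpretability of the harms table. The primary outcome and sample size are not touched.

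**Working it through.** The plan gives no figure for harms ascertainment, so there is none to reproduce.

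**1. Scheduled post-randomisation occasions up to week 8**

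| Source | SHAPE | Waitlist | Where stated |
|---|---|---|---|
| Questionnaires | 8 (weeks 1–7 and week 8) | 2 (weeks 4 and 8) | Secondary outcome measures; Fig. 2 caption |
| Coaching calls | about 6 (up to 8) | 0 | SHAPE condition; Waitlist condition |
| SCID-5 | 1 (week 8) | 1 (week 8) | Plans for assessment and collection of trial data |
| Total | 15 (up to 17) | 3 | |

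Ratio: 15/3 = 5.0, or 17/3 = 5.7. The waitlist's baseline assessment precedes randomisation and does not count. The harms sentence could be read as placing a SCID-5 at week 4, but the data collection section lists the SCID-5 only at baseline, 8 weeks and 6 months. Even with a week-4 SCID-5 the ratio would be 15/4 = 3.75.

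**2. What this could do to detection, on questionnaires alone**

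Assumptions, none of them from the documents: true risk is equal in both arms; onset is uniform over 8 weeks; an event lasts L weeks; each questionnaire falling within it picks it up independently with probability q. With k such questionnaires, detection is 1 − (1 − q)^k. SHAPE has questionnaires at weeks 1 to 8, the waitlist at weeks 4 and 8.

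- L = 1: SHAPE q; waitlist q/4.
- L = 2: SHAPE (7/8)[1 − (1 − q)²] + q/8; waitlist q/2.
- L = 4: SHAPE (5/8)[1 − (1 − q)⁴] + (1/8){[1 − (1 − q)³] + [1 − (1 − q)²] + q}; waitlist q.
- L = 8: SHAPE is the mean of 1 − (1 − q)^k over k = 1 to 8; waitlist ½[1 − (1 − q)²] + ½q.

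Ratio of detection, SHAPE to waitlist:

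| Duration | q = 0.3 | q = 0.5 | q = 0.8 |
|---|---|---|---|
| 1 week | 4.0 | 4.0 | 4.0 |
| 2 weeks | 0.484/0.150 = 3.2 | 0.719/0.250 = 2.9 | 0.940/0.400 = 2.4 |
| 4 weeks | 0.658/0.300 = 2.2 | 0.852/0.500 = 1.7 | 0.968/0.800 = 1.2 |
| 8 weeks | 0.725/0.405 = 1.8 | 0.876/0.625 = 1.4 | 0.969/0.880 = 1.1 |

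A recall window acts like a longer event: with one week of recall, a 1-week event behaves like a 2-week one. Coaching calls are left out and would add to SHAPE detection only.

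**3. Illustration in counts**

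Take 46 per arm (Sample size), an assumed true risk of 30%, L = 2 and q = 0.5. Expected true events are 46 × 0.30 = 13.8 per arm. Recorded: 13.8 × 0.719 = 9.9 in SHAPE and 13.8 × 0.250 = 3.5 on the waitlist, with no real difference.

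**The case against.** Several objections have force.

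- **AEs are not excluded from publication.** A reader might infer that only SAEs will be published. The text does not say so: it commits to SAEs and is silent on AEs, and it restricts reporting to SAEs only for the steering committee. The AE appendix and the SAP are not shown and may add AE tables.
- **No between-arm harms comparison is promised.** True. The bias arises once counts are shown or read by arm.
- **SAEs depend less on contact frequency.** Also true. The distortion falls mainly on brief, non-serious events, the category for which no publication commitment is stated.
- **Some routes are open to both arms.** All participants have the team's contact details. New traumatic events are asked about at weeks 4 and 8, service use is collected at week 8, and urgent concomitant treatment is documented. These narrow the gap but do not equalise the scheduled routes.
- **Symptom worsening is not invisible.** PCL-5, PHQ-9 and GAD-7 are compared at weeks 4 and 8 on a common schedule, although mean differences do not show individual deterioration.
- **Extra contact is inherent in coaching versus waiting.** Agreed, which is why the remedy concerns reporting.

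It is also tempting to treat the 15 and 3 occasions as independent looks at an event present throughout, using 1 − (1 − p)^15 against 1 − (1 − p)^3. That gives ratios of 2.9, 2.0 and 1.5 for p = 0.1, 0.2 and 0.3. The documents do not support it: weekly forms feed the next call, a rise in PHQ-9 item 9 prompts the coach's risk assessment, and later-onset events get fewer looks.

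**Conclusion.** The point holds as a minor one. Unequal ascertainment is stated outright, at about 15 scheduled occasions against 3, and nothing in the article corrects for it. Any by-arm comparison of recorded harms would lean towards more events in SHAPE. The direction follows from the schedule. The size does not: roughly 1.1- to 4-fold on questionnaires alone, depending on assumed event duration and reporting probability, and probably smaller for SAEs.

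The documents do not support going further. They do not say that AEs will be withheld, that AEs form most of the harms information, or that worsening is the likeliest harm of this intervention.

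**What to change.** Replace the publication sentence in the section on adverse event reporting and harms with a rule that:

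1. reports AEs and SAEs by randomised arm for the 8-week randomised period, with later events, including those during post-waitlist SHAPE, shown separately;
2. bases the between-arm comparison on sources common to both arms, namely the week-4 and week-8 questionnaires (including PHQ-9 item 9) and the week-8 SCID-5, counting an event evident there even if a coach already knew of it;
3. lists events found only through weekly forms or coaching calls separately, with a statement that ascertainment differed between arms.

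No contact schedule or risk procedure changes, which suits a trial whose recruitment is complete. The cost is one extra table from logged data and fewer events in the like-for-like comparison. It assumes that the forms or log show when and how each event was found. If they do not, that must be recovered from the source records, or the limitation stated.

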### Participant timeline {18}

A summary and timeline of the administration time points for forms, measures, interventions, and assessments administered in the RCT is shown in Fig. 2.

**Fig. 2 Fig2:**
[figure not shown]
Schedule for forms, measures, interventions, and assessments in the SHAPE randomised controlled trial. *6 months post-intervention for participants randomly allocated to intervention or to waitlist who then receive the intervention, or 6 months post-waitlist for participants who complete the waitlist and who do not take up the intervention. **Followed by SHAPE intervention for participants who complete the waitlist condition and who would like to receive SHAPE coaching. ***Every week participants in SHAPE coaching receive a short weekly questionnaire (i.e. PCL-5 and PHQ-9) except in week 4 when they are sent the mid-intervention questionnaire. Informed consent-1 = Informed consent for eligibility assessment; *PCL-5* = PTSD Checklist for DSM-5; *PHQ-9* = Patient Health Questionnaire; *SCID-5* = Structured Clinical Interview for DSM-5 (PTSD and MDD modules); Informed consent-2 = Informed consent for assessment/trial; *GAD-7* = Generalised Anxiety Disorder Scale; *ISI* = Insomnia Sleep Index; *PTCI-s* = Posttraumatic Cognitions Inventory short version; *RIQ-s* = Responses to Intrusions Questionnaire short version; *LEC-5* = Life Events Checklist for DSM-5; *ITQ* = International Trauma Questionnaire; *ACE-Q* = Adverse Childhood Experiences Revised Questionnaire; *WEMWBS* = Warwick-Edinburgh Mental Wellbeing Scale; *CD-RISC-25* = Connor-Davidson Resilience Scale 25; *iPCQ* = iMTA Productivity Cost Questionnaire; *SF-HLQ* = Short Form Health and Labour Questionnaire; *CSRI* = Client Service Receipt Inventory; *EQ-5D-5L* = EuroQol-5 Dimensions-5 Levels health survey; *Re-QoL* = Recovering Quality of Life Questionnaire

#### SHAPE condition timeline

Participants receiving the SHAPE coaching will be sent the PCL-5 and PHQ-9 at the end of each week to assess for changes in symptoms of PTSD and MDD respectively and to help in planning the upcoming coaching call. These measures will be sent via a secure online link for participants to complete on a digital device. Participants will need to enter their unique ID number before completing the self-report measures to allow the research team to link IDs to responses. Halfway through the intervention, participants will receive a longer set of measures to complete. Eight weeks after randomisation, participants will complete a longer set of post-intervention questionnaires and have another SCID-5 telephone assessment to re-assess for PTSD and MDD. Six months after receiving the SHAPE intervention, a final set of follow-up questionnaires will be sent, and participants will have a final remote SCID-5 telephone assessment to re-assess for PTSD and MDD. All post-randomisation SCID-5 assessments will be conducted by blinded assessors, unaware of the participant's allocation.

